# HIPTox—Hazard Identification Platform to Assess the Health Impacts from Indoor and Outdoor Air Pollutant Exposures, through Mechanistic Toxicology: A Single-Centre Double-Blind Human Exposure Trial Protocol

**DOI:** 10.3390/ijerph21030284

**Published:** 2024-02-29

**Keywords:** air pollution, cognitive function, dementia, indoor air, human exposure, study protocol

## Abstract

Over the past decade, our understanding of the impact of air pollution on short- and long-term population health has advanced considerably, focusing on adverse effects on cardiovascular and respiratory systems. There is, however, increasing evidence that air pollution exposures affect cognitive function, particularly in susceptible groups. Our study seeks to assess and hazard rank the cognitive effects of prevalent indoor and outdoor pollutants through a single-centre investigation on the cognitive functioning of healthy human volunteers aged 50 and above with a familial predisposition to dementia. Participants will all undertake five sequential controlled exposures. The sources of the air pollution exposures are wood smoke, diesel exhaust, cleaning products, and cooking emissions, with clean air serving as the control. Pre- and post-exposure spirometry, nasal lavage, blood sampling, and cognitive assessments will be performed. Repeated testing pre and post exposure to controlled levels of pollutants will allow for the identification of acute changes in functioning as well as the detection of peripheral markers of neuroinflammation and neuronal toxicity. This comprehensive approach enables the identification of the most hazardous components in indoor and outdoor air pollutants and further understanding of the pathways contributing to neurodegenerative diseases. The results of this project have the potential to facilitate greater refinement in policy, emphasizing health-relevant pollutants and providing details to aid mitigation against pollutant-associated health risks.

## 1. Introduction

### 1.1. Background and Rationale

Air pollution is the primary global environmental risk to health that increases mortality worldwide [1]. Adverse effects of low-quality air on cardiovascular and respiratory systems are well-established [2,3], with our understanding of its effects on both short- and long-term population health advancing considerably over the last decade. There is also growing evidence that air pollution is neurotoxic [4,5], degrading the brain’s cellular structures [6], leading to neurocognitive decline [7] and delaying neurocognitive development [8]. However, there are still major gaps in our understanding of the most harmful components within the air we breathe and the mechanisms by which they induce adverse effects [9].

Lifetime exposure to low-quality air has been linked to greater risk of substantial cognitive deficits associated with progressive neurodegenerative diseases such as Alzheimer’s Disease [10], Parkinson’s Disease [11], and Multiple Sclerosis [12]. Chronic exposure to low-quality air is also associated with poorer than expected memory [13,14,15,16], psychomotor and sensory processing [17], and cognitive executive function [18,19] in clinically healthy children. Short-term episodes of exposure to low-quality air have also shown impact on these cognitive functions [20,21,22,23]. Evidence is, however, mixed with regards to the impact of certain pollutant mixtures on different cognitive domains [7]. It is therefore critical to assess a range of cognitive functions and changes as a function of differing common sources of air pollution.

Air pollution may manifest its acute and chronic impacts on the brain via direct interaction of inhaled particles, or desorbed chemical constituents, with non-neuronal glial cells and neurons in the brain, based either on their uptake via translocation along olfactory neurons to the olfactory bulb [24]; or their entry across the blood brain barrier from the circulation [25]. This has been supported by evidence of combustion-like nanoparticles in the brains of sentinel animals and humans from polluted environments [26], associated in autopsy samples with histopathological features of early dementia, microglia immune defence activation, and neuronal injury [27]. A second hypothesis proposes that the neurological damage reflects an indirect impact of air pollution induced systemic inflammation and its transmission to the brain across the glial-neurovascular unit [28,29]. There is therefore a clear necessity for this study to investigate evidence for both routes through both collection of blood to measure traditional toxicity endpoints, including pro-inflammatory biomarkers and markers for organ specific toxicity, and nasal lining fluids to identify the presence of neuronal injury markers.

We believe there is a strong need to respond to the emerging evidence of the impact of air pollution on the brain across the life course, from early life cognitive delays [14] to adverse mental health [30] and dementia risk. Moreover, the estimated cost of air pollution is GBP 20 billion per year in the UK, specifically attributable to cardiopulmonary mortality and morbidity alone [31]. The neurological effects carry significant economic and societal risks, above and beyond the cardiopulmonary risks, and will likely increase the economic and societal cost significantly. An enhanced understanding of which components of the air are drivers of these adverse neurological effects and the underlying causal mechanisms are, therefore, questions of fundamental importance to the health and economics of the nation.

The presented single-centre double-blind human exposure trial will investigate the effect of exposure to four common air pollutants deriving from cleaning products, diesel exhaust, cooking emissions, and wood smoke on cognitive function comparative to clear air. Pollutants from different sources display diverse physical and chemical properties, potentially resulting in a range of cognitive effects. For example, black carbon is the primary compound in particles emitted from engines and wood combustion during the flaming phase, often characterised by irregular shapes [32]. Conversely, organic compounds dominate aerosols from cleaning products [33], cooking emissions, and wood combustion during the smouldering phase, predominantly exhibiting spherical shapes [32,34]. Furthermore, the chemical composition and volatility of organic aerosols vary among sources, likely contributing to differences in cognitive effects. Therefore, the selected exposures not only contribute substantial fractions to indoor and outdoor air but also exhibit a range of physicochemical properties. The evidence for their influence on cognitive health is described in Section 2.4. The data generated from these human exposures represent an initial step in understanding the most hazardous components of outdoor and indoor air pollutants. This research aims to lay the groundwork for elucidating the causal pathways contributing to the development and exacerbation of neurodegenerative diseases. The results of this project will facilitate greater refinement in policy to place greater emphasis on health-relevant pollutants and provide these details to aid mitigation against pollutant-associated health risks.

### 1.2. Objectives

The primary objective of this study is to rank the acute effects of a range of air pollution exposures on cognitive function in healthy aged individuals with a family history of increased dementia risk.

The secondary objective of this study is to identify evidence of changes in inflammatory or immune signals post exposure to pollutants compared to clean air, exploring possible underlying mechanisms of any identified cognitive changes.

## 2. Methodology

### 2.1. Trial Design

This is a single-centre double-blind study of the effects of mixed air pollutants on the cognitive function of healthy human volunteers with a family history of increased risk of dementia. Participants will all undertake sequential controlled exposures to four air pollutants and clean air as control exposure, i.e., a repeated measures design. Cognitive testing, biological sampling, and physiological tests will be carried out before and after each exposure. The study design is outlined in Figure 1.

### 2.2. Study Setting

The HIPTox study will be carried out at the NIHR/Wellcome Trust Clinical Research Facility (MCRF), [name] and the Manchester Aerosol Chamber (MAC), [name].

### 2.3. Participant Volunteers

This study will aim to recruit 45 clinically healthy individuals aged 50 and above with a family history of dementia. See Appendix A for full inclusion and exclusion criteria. Recruitment began in May 2023 and due to significant challenges, as explained in detail in the discussion section, the originally planned sample size was reduced to 15 participants. The study is currently ongoing, and data collection is expected to be completed by the end of 2023. See Table 1 for study timeline.

#### 2.3.1. Power Calculation

Based on effect size and variance from a currently unpublished study [35] looking at cognitive load and attention (measured as change in response time (
Δ
RT) after Diesel Exhaust exposure (
Δ
RT = 22 ms, s.d. = 25 ms), a sample size of 30 subjects will have 90% power to detect significant response time changes of 15 ms assuming the standard significance level of *p* < 0.05. We acknowledge this current study is a different design utilising an older adult population and have, therefore, calculated for a slightly smaller effect size than that of the previous study to compensate for larger RT variance in older adults. As longitudinal studies are prone to extensive participant attrition, the sample size of 45 aims to allow full data to be collected for a minimum of 30 participants. Power calculations were performed using PS [36].

In response to recruitment challenges, we revised the sample size, prompting a re-exploration of the sample size estimate and power calculation to identify the minimum sample likely to yield valuable results. The proposed study design involves comparing the impact of four pollution exposures by examining the differences between pre- and post-exposure measurements relative to baseline measurements. The independent design from the previous study, featuring one measure per group, makes it unfeasible to extrapolate data. Therefore, under the assumption of a conservative correlation among repeated measures set at 0.5, a minimum sample size of 11 participants is needed to achieve 90% power in detecting a moderate (0.45) effect size at a significance level of 0.05.

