### 2.7. Data Analysis

Data generated by this study will be analysed using longitudinal statistical modelling designed to account for the repeat measures in individual subjects (e.g., general estimating equation or random effects modelling, depending on the extent and nature of any missing or partial data). This will describe and account for changes in pre-exposure measures over time, comparing the effects of the different air pollution exposures to the clean air control.

Cognitive subscales will be entered into this process separately, to aid in pairing aerosols with undesirable changes identified in each cognitive domain. Our goal is to ensure an equal representation of biologically male and female participants, acknowledging potential sex-dependent effects of exposure. Consequently, biological sex will be entered as a covariate of interest during analysis.

In addition to ranking cognitive impacts in relation to the exposure sources, these data will be related to biomarkers of systemic and neuro-inflammation/injury to test the secondary hypothesis that acute cognitive effects and more severe downstream neurological impacts reflect underlying inflammatory processes.

Specifically, our primary and secondary end points are as follows:

Primary end point:

Evidence of impairment in cognitive function post exposure as measured by any of these cognitive tasks compared to clean air:Difference in the Approach bias measured via the Expression Recognition Task post pollutant exposure;Change in the Cognitive Control response time post pollutant exposure;Change in the 2-back discrimination index post pollutant exposure.

Secondary end point:

Change in performance on any of these cognitive tasks post pollutant exposure compared to clean air:Psychomotor Vigilance Task;Purdue Pegboard Test;Evidence of inflammatory or immune signals post exposure to pollutants compared to clean air;Change in lung function post pollutant exposure compared to clean air;Change in DNA post pollutant exposure compared to clean air.

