## 3. Discussion

Using an integration of cognitive psychology, atmospheric sciences, clinical experimental medicine, and clinical biochemistry, this project aims to assess the comparative impact of source-specific aerosols on physiological and cognitive functioning. The methodology involves repeated testing pre and post exposure to controlled levels of pollutants, enabling the identification of acute changes in functioning and the detection of peripheral markers of neuroinflammation and neuronal injury.

We initially aimed for 45 participants; however, various recruitment challenges emerged during the study, such as the extended study duration, time-intensive visits, and the eligibility of those in the specific cohort of participants required. Despite efforts to alleviate the burden on participants through protocol reviews and an extensive recruitment drive involving over 45 Patient and Public Involvement and Engagement (PPIE) interactions, it became apparent that recruiting 45 participants was not feasible.

Upon reassessment, the study team adjusted the target to a smaller sample size of 15, assuming a similar dropout rate (33%). This adjustment was made to still maintain sufficient data for reasonable statistical power. Despite this adaptation, we acknowledge that the reduction in statistical power increases the likelihood of not detecting a true effect, leading to a higher risk of committing a Type II error due to wider confidence intervals. Detecting small effects is also challenging due to queries associated with using a shorter exposure time and concentrations relative to previous studies. Similarly, a smaller sample size is more susceptible to random fluctuations, which are anticipated in cognitive functioning. However, the repeated-measures design and control of participant activities during data collection aim to reduce this as a confounding variable.

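### Primary endpoints are worded as pre-to-post change and no pre-exposure covariate is named; analysed unadjusted, a contrast with clean air could have up to twice the variance it needs

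*Protocol article*

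**What the plan says.** The revised power calculation in section 2.3.1 describes the comparison as "comparing the impact of four pollution exposures by examining the differences between pre- and post-exposure measurements relative to baseline measurements". It proceeds "under the assumption of a conservative correlation among repeated measures set at 0.5" and concludes, with alpha at 0.05, that "a minimum sample size of 11 participants is needed to achieve 90% power in detecting a moderate (0.45) effect size at a significance level of" that size. It does not say which measures the correlation links, nor on what scale the effect size is expressed.

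Section 2.7 lists three primary endpoints, all compared with clean air. One reads "Change in the Cognitive Control response time post pollutant exposure"; the 2-back discrimination index is worded the same way. The third, approach bias, is worded as a difference rather than a change.

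For the model, section 2.7 names GEE or random effects and leaves the choice to depend on missing data. It adds: "This will describe and account for changes in pre-exposure measures over time". Biological sex is the only covariate it names. Section 2.4 confirms that pre- and post-exposure measures are taken for every air mixture, clean air included.

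**The concern.** In a parallel-group trial, change from baseline removes stable differences between people. Here the comparison of a pollutant session with the clean-air session, within the same person, already does that. What the same-session pre-exposure score can still remove is variation specific to the day. If that variation is modest, subtracting the score with weight 1 brings in its measurement noise twice, once for the pollutant and once for clean air. Using the score as a covariate lets the data set the weight.

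Precision is scarce. The target fell from 45 to 15 with 33% dropout assumed (section 3), which leaves about 15 × 0.67 = 10 completers. The primary objective is to rank exposures, and a ranking depends on precise contrasts. Doubling the variance of a contrast has the same effect on its standard error as halving the number of participants.

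**Working it through.** **The plan's own figures.** The first calculation uses "RT = 22 ms, s.d. = 25 ms" and states that "a sample size of 30 subjects will have 90% power to detect significant response time changes of 15 ms". The paired normal formula gives (25 × (1.960 + 1.282) / 15)² = 29.2, so 30; noncentral-t power at 30 is 88.8%, close to the stated 90%.

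The revised 11 reproduces as a one-group repeated-measures F test with m = 4 measures, Cohen's f = 0.45, ρ = 0.5 and sphericity:

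- λ = f² × N × m / (1 − ρ) = 0.2025 × 11 × 4 / 0.5 = 17.82, on 3 and 30 degrees of freedom, gives power 92.8%.
- N = 10 gives 89.6%, so 11 is the smallest N reaching 90%. With m = 5 the answer would be 9.

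This suggests, without proving it, that 0.5 was applied across four exposure-specific difference scores.

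**Variance of the contrast.** Let D_pre and D_post be a participant's pollutant-minus-clean-air differences in the pre and post scores, each with variance V, and let r be their correlation.

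- Unadjusted change: Var(D_post − D_pre) = 2V(1 − r).
- Adjusted for the pre score: V(1 − r²).
- Ratio: 2(1 − r) / [(1 − r)(1 + r)] = 2/(1 + r).

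For r between 0 and 1 the ratio lies between 2 and 1.

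**Putting numbers in.** Set the raw-score SD to 1, correlation b between scores from different sessions, and w between pre and post in the same session. Then V = 2(1 − b) and r = (w − b)/(1 − b). With b = 0.5, V = 1. The values of b and w are assumptions; the documents give neither.

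| w | r | change | adjusted | variance ratio | SE ratio |
|---|---|---|---|---|---|
| 0.5 | 0 | 2.00 | 1.00 | 2.00 | 1.41 |
| 0.6 | 0.2 | 1.60 | 0.96 | 1.67 | 1.29 |
| 0.7 | 0.4 | 1.20 | 0.84 | 1.43 | 1.20 |
| 0.8 | 0.6 | 0.80 | 0.64 | 1.25 | 1.12 |
| 0.9 | 0.8 | 0.40 | 0.36 | 1.11 | 1.05 |

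The first row has one common correlation. Whenever w = b, r is 0 and the ratio is 2, whatever the common value; the factor 2 does not come from 0.5.

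**Cost of estimating the slope at n = 11** (simulation, 6,000 replicates). With all correlations 0.5 the ratio is 1.93 when the slope is pooled over five exposures and 1.77 from a single pair. With w = 0.75 it is 1.32 and 1.18. With w = 0.9 it is 1.08 and 0.97, so the gain is then negligible, or slightly negative from one pair alone.

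**The case against.** The strongest reply is that the plan does not commit to an unadjusted change score. Section 2.7 leaves the model open, and its sentence about accounting for pre-exposure measures can be read as allowing adjustment. A change endpoint can also be analysed with the pre score as covariate, which removes the penalty. The third primary endpoint is not worded as change, and covariates are commonly left to an analysis plan that is not shown here. All of this stands. It limits the point to a conditional loss of efficiency; no error has been shown and bias is not at issue. The point remains worth making because the article does state a construction based on differences and names sex, but not the pre score, as a covariate.

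Same-session scores may also be more alike than scores from sessions at least two weeks apart. That stands too, and is why the size is given as a range.

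A reader might go further and infer that the plan's own 0.5 doubles the variance, or that power at 11 participants for an effect of 0.45 is about 18% with change scores against 31% with adjustment. The documents support neither. The 0.5 is not said to link pre with post. If it linked all raw scores equally, change scores from different sessions would have covariance 0.5 − 0.5 − 0.5 + 0.5 = 0, and the same F calculation with ρ = 0 would need 19 participants, not 11. The power figures need 0.45 to be a mean difference in raw-score SDs and about 40 residual degrees of freedom. The plan states neither, and its 11 reproduces with 0.45 as Cohen's f.

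**Conclusion.** The point holds as a possible loss of precision. If the change endpoints are analysed without the pre-exposure score as a covariate, each contrast with clean air has up to twice the variance of the adjusted contrast. The ratio is exactly 2 when all raw scores share one correlation, and about 1.67 to 1.11 for between-session correlation 0.5 and same-session correlation 0.6 to 0.9.

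This rests on equal variances before and after exposure, on r not being negative, and on an assumed range of correlations. The ratios are large-sample values; at 11 participants the gain is somewhat smaller. No ratio or power figure here should be attributed to the plan.

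**What to change.** State in section 2.7 that the primary analysis models the post-exposure score in a mixed model with exposure, session number, sex, the same-session pre-exposure score and the participant's mean pre-exposure score, plus a participant random intercept. Including the mean separates the within-person slope from the between-person slope; the within-person slope is the one that matters for these contrasts. Modelling the change with the same covariates gives the same exposure contrasts, so the endpoint wording can stay. Report the contrasts with clean air as adjusted differences and show raw change scores descriptively. The session term presumes that exposure order differs between participants.

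In section 2.3.1, say which measures the 0.5 links.

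The cost is wording and one or two model degrees of freedom in a small sample, with no new data. Little is gained for outcomes whose same-session correlation is very high, so extension to spirometry or biomarkers should be decided outcome by outcome.

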#### 2.3.2. Patient and Public Involvement and Engagement (PPIE)

This project was supported by the Manchester University Foundation Trust’s public and patient engagement team (VOCALS) during the study conception and funding approval. Numerous public and patient engagement activities were carried out prior to protocol finalisation. These events helped shape the final study design including duration of the study. During the recruitment phase, we continued to engage with patients and the public via over 45 engagement events, including “Brain Health Day, Manchester”, local workshops, and pollution awareness events. We aim to carry out a post study completion engagement event with all the participants to disseminate the results alongside publication in scientific journals.

#### 2.3.3. Recruitment

Participants will be recruited from the general public. Volunteers who are employees of The University of Manchester or Manchester University NHS Foundation Trust will be permitted to take part if not involved with the project. Advertisement posters will be placed in public spaces including local community groups, places of worship, and NHS and university buildings. Social media advertisements will be run using official accounts of the University of Manchester, NHS Manchester Foundation Trust, and Research for the Future. We will also contact participants who have previously given permission to be contacted for research studies. Due to potential sex-dependent effects of aerosol exposure, we aim to collect equal numbers of biologically male and female participants.

To promote participant retention, participant payment will increase each visit so that there is an increasing incentive to continue participation as the study continues. Informal participant feedback will be collected each visit to improve subsequent visit comfort and amend the protocol as necessary. Data from those who discontinue participation, whether through personal withdrawal or change in eligibility, will be included in data analysis where inclusion of partial data is possible.

